# High-intensity exercise prescription guided by heart rate variability in breast cancer patients: a study protocol for a randomized controlled trial

**DOI:** 10.1186/s13102-023-00634-2

**Published:** 2023-03-08

**Keywords:** Breast cancer survivors, HIT, Strength training, Remote and supervised exercise, Cardiotoxicity, Physical effects, Psychosocial effects

## Abstract

**Background:**

Breast cancer is a chronic disease with a large growth in its treatments, prognosis, improvements, side effects and rehabilitation therapies research. These advances have also highlighted the need to use physical exercise as a countermeasure to reduce the cardiotoxicity of pharmacological treatments, increase patients' strength and quality of life and improve body composition, physical condition and mental health. However, new investigations show the need for a closed exercise individualisation to produce higher physiological, physical and psychological benefits in remote exercise programs. To this end, the present study will use, in a novel way in this population, heart rate variability (HRV) as a measure for prescribing high-intensity training. Thus, the primary objective of this randomised clinical trial is to analyse the effects of a high-intensity exercise program daily guided by HRV, a preplanned moderate to high-intensity exercise intervention and a usual care group, in breast cancer patients after chemotherapy and radiotherapy treatments.

**Methods:**

For this purpose, a 16-week intervention will be carried out with 90 breast cancer patients distributed in 3 groups (a control group, a moderate to high-intensity preplanned exercise group and a high-intensity exercise group guided by HRV). Both physical exercise interventions will be developed remotely and supervised including strength and cardiovascular exercises. Physiological variables, such as cardiotoxicity, biomarkers, lipid profile, glucose, heart rate and blood pressure; physical measures like cardiorespiratory capacity, strength, flexibility, agility, balance and body composition; and psychosocial variables, as health-related quality of life, fatigue, functionality, self-esteem, movement fear, physical exercise level, anxiety and depression will be measure before, after the intervention and 3 and 6 months follow up.

**Discussion:**

Personalized high-intensity exercise could be a promising exercise intervention in contrast to moderate-intensity or usual care in breast cancer patients to reach higher clinical, physical and mental effects. In addition, the novelty of controlling HRV measures daily may reflect exercise effects and patients' adaptation in the preplanned exercise group and a new opportunity to adjust intensity. Moreover, findings may support the effectiveness and security of physical exercise remotely supervised, although with high-intensity exercise, to reach cardiotoxicity improvements and increase physical and psychosocial variables after breast cancer treatments.

*Trial registration* ClinicalTrials.gov nº NCT05040867 (https://clinicaltrials.gov/ct2/show/record/NCT05040867).

**Supplementary Information:**

The online version contains supplementary material available at 10.1186/s13102-023-00634-2.

## Background

Worldwide cancer incidence is growing each year reaching 19.3 million new cancer cases in 2020. Whereas it is expected to worsen to 28.4 million cases in 2040, an increase of 47%. Concretely, female breast cancer has surpassed lung cancer as the most diagnosed type, with an estimated 2.3 million new cases every year (11.7%), accounting for 1 in 4 cancer cases and being the fifth leading cause of cancer mortality worldwide, with 685,000 yearly deaths. However, although new advances and treatments are increasing cancer-related survivorship, estimated to be 29.1% higher in 2029 [1], breast cancer survivors had an almost twofold higher risk of dying compared with cancer-free women [2]. An aspect to consider given that by 2040 it is expected that 73% of survivors will be over 65 years of age [1].

One of the principal causes of these differences leads to cancer and treatments side-effects in breast cancer survivors increasing their comorbidity rates and decreasing patients' health-related quality of life (HRQoL) and survivorship [3]. Regarding long-term side effects, breast cancer patients may suffer, even several years after the diagnosis, cardiotoxicity [4], autonomic dysfunction[5], sarcopenia [6, 7], joint pain and cancer-related fatigue [8], among others, are quite common and severe. These interrelated consequences, caused among other aspects by pharmacological toxicity [6, 9] and physical inactivity, are associated with mortality [10–12], worse prognosis and cancer evolution [13, 14] and morbidity [15]. Cardiotoxicity, the toxic effect produced in patients' cardiovascular system by some anticancer drugs, could cause the appearance of several cardiovascular abnormalities such as hypotension or hypertension, cardiorespiratory capacity decline, arrhythmias, myocardial infarction, thromboembolism, myocarditis, greater arterial rigidity, over-activation of the sympathetic nervous system and a parasympathetic decline -measured by heart rate variability (HRV)-[16–18]. Such is its gravity, that breast cancer survivors are at high risk of heart failure [19], autonomic dysfunction [20] and cardiovascular disease [19] up to the point of being the second most common cause of death among breast cancer survivors [21].

However, physical exercise programs, as recent literature is showing, could be an effective tool to reduce these severe side effects [22]. Although the investigations performed in breast cancer patients, not murine models, are limited it seems that exercise may increase left ventricular ejection fraction and cardiorespiratory capacity [23], decrease biomarkers such as Brain Natriuretic Peptide (BNP), high-sensitivity cardiac troponin and c-reactive protein [22, 24, 25] and blood pressure, and improve the sympathovagal imbalance increasing baroreflex sensibility and reducing resting heart rate [26, 27]. These physiological changes have been proved to be produced specially by endurance training due to DOX-induced increases in oxidative stress and apoptosis, decreases chronic inflammation, angiotensin II, renin and atherosclerosis and increases the patient's vasodilatation [25]. To reach the mentioned effects it seems that exercise programs focused on cardiotoxicity need to involve at least 36 sessions [24]. The exercise intensity carried out in the interventions is quite heterogeneous involving most of them from moderate to high intensity [22, 24, 25]. Whereas, more current research, but not focused on cardiotoxicity, has found also positive psychosocial, physical and physiological effects with high-intensity exercise interventions [23, 26] and it seems to be a potential tool to provide a higher glycolytic metabolism [28], induce a decrease of intratumorally lactate concentration [29] and moderate the overexpression of reactive oxygen species limiting the tumor growth or cancer recurrence and inflammation [30].

Nevertheless, most of the interventions focused their exercise programs only on aerobic training forgetting the role of muscle mass and function to reduce the toxicity produced by treatments and tumor prognosis [6], even though sarcopenia is associated with an increased risk of overall mortality in breast cancer survivors and breast-cancer-specific mortality [11, 31, 32]. In this regard, resistance training interventions have been stated to be crucial to recovering the loss of muscle mass and muscle function caused by chemotherapy [33, 34], reducing myomatosis and chronic inflammation [35], reducing oxidative free radicals and oxidative stress [35], improving body composition [36], reducing pain join and cancer rated fatigue [37], increasing cardiorespiratory fitness [23, 38] and HRQoL [37], reducing mortality from cardiovascular disease [39] and all causes of death [40]. Commonly, resistance programs, performed alone or like concurrent training, lasted at least 12 weeks, utilized a moderate intensity, between 50 and 80% of 1 repetition maximum (RM) or high intensity < 85% of 1 RM [36, 37].

The debate and the controversial results about optimal exercise intensity and type for breast cancer survivors could be produced due to cancer investigation and clinical practice, especially in group-based programs, all the participants from the same group train at the same corresponding intensity. In this regard, programs are not daily personalized without considering participants' daily physiological and psychological requirements. So that, those participants who do not respond correctly to high-intensity programs could be because they do not tolerate the pre-planned intensity equally every day. Innovative investigations in sports sciences are starting to prescribe daily training intensity by utilizing participants' matutine heart rate variability [39] a new useful tool not employed before, as far as we are concerned, in breast cancer survivors. HRV provides a multidimensional registration of autonomic modulation [40] presenting the physiological stress and the sympathovagal imbalance, so common in breast cancer survivors [5]. Besides, some investigations have stated the relation between pain perception, so common in breast cancer patients, and HRV scorings, showing that people with high pain have lower parasympathetic parameters [41]. For these reasons, the current study will aim to prescribe high-intensity exercise involving cardiovascular and resistance training, guided daily by HRV trying to individualize exercise to patients’ physiological stress.

Moreover, concerning the new habits and the current risk due to the coronavirus pandemic (COVID-19) there is a need for novel intervention in a supervised and remote-controlled context. In this sense, it could be also one of the first exercise programs where the physical specialist control and monitor each exercise session in real-time in contrast to most remote interventions based on self-delivery exercise, physical exercise recommendations or mobile apps [42].

### Aim and research questions

Therefore, given the potential benefits of physical exercise and the possibilities of optimizing how it is prescribed for cancer patients, the current randomized controlled trial aims to analyze the effectiveness of a high-intensity remote exercise program guided daily by HRV compared to a pre-planned remote moderate to high-intensity exercise program in breast cancer survivors. For this purpose, the effects of both physical exercise programs on physiological (cardiotoxicity, inflammatory factors, cardiovascular variables, body composition and anthropometric parameters), physical (low and upper body strength, cardiorespiratory fitness, low and upper body flexibility, agility and balance) and psychological health (HRQoL, fatigue, life satisfaction, self-esteem, anxiety and depression, shoulder disability perception, physical activity, kinesophobia and exercise motivation) measurements of breast cancer patients will be assessed and compared an inactive control group.

## Methods/design

### Study design

The research will be conducted following the Helsinki declaration [43] and the American Society of Clinical Oncology policy statement [44]. Patients will be randomly assigned to three groups where two of them will participate in a physical exercise intervention and the left group will continue with usual care for 16 weeks (see Fig. 1). Moreover, the study methods described below follow the Standard Protocol Items Recommendations for Interventional Trials (SPIRIT) of 2013 [45] (SPIRT schedule and checklist are shown in the Additional file 1). After the positive response from the ethics committees, the trial was registered at ClinicalTrials.gov, recognized by the World Health Organization and the International Committee of Medical Journal Editors, under the identification number of NCT05040867.

**Fig. 1 Fig1:**
[figure not shown]
Study protocol timeline

### Participants

#### Recruitment and eligibility

A total of 90 patients are being recruited from the Oncology Service of Cantabria, concretely, they are being enrolled in the University Hospital of Marqués de Valdecilla. The enrolment consists of two phases. First, an oncologist and a radiologist select patients who fulfill the following inclusion criteria: (a) women aged between 18 and 65 years, (b) having luminal or triple-negative breast cancer, (c) having received and finished chemotherapy and radiotherapy treatment. In addition, patients are excluded if: (a) they have been scheduled for surgery during the study (b) they have HER2 + breast cancer, (c) they have severe heart disease before chemotherapy, (d) they have finished the cancer treatment more than 5 months ago, (e) they have metastatic cancer, (f) they have any injury which prevents them to perform the intervention or the evaluation correctly, (g) they have severe psychiatric illnesses.

In the second phase, patients are called to the hospital by the oncologist and the physical exercise professional to explain in detail the study and each intervention group requirement. After answering patients’ questions and asking for some technical needs for mobile phone application licenses, a complete description of the study is given to the participants.

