#### Randomization and allocation

The study is a blinded, randomized, controlled trial. Before baseline assessments, participants are randomly assigned to one of the three groups: a group that performs the planned physical exercise program based on daily heart rate variability (HRVG), a group that performs the conventional pre-planned physical exercise program (PEG) and a control group (CG).

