##### Pre-planned remote moderate to high-intensity physical exercise program

The current exercise group will perform exercise following the recommendations of several and important literature such as the American College of Sports Medicine guidelines carrying the exercise with an intensity going from moderate to high intensity. Concretely in the cardiovascular exercise, the participant will start with an intensity of 65% of their reserve HR, in the first mesocycle; and will end with an intensity of 80% of their reserve HR. In the resistance exercise, they will commence lifting weights corresponding to their 55% RM and finish in the last mesocycle lifting loads matching their 70% RM.

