##### High-intensity remote physical exercise program guided daily by HRV

Although all participants will daily measure their HRV, only in this intervention group each day's results will influence their exercise intensity. From the outcomes reported with smartphone photoplethysmography, explained the measurement process in the outcomes part, the root means squared differences of successive RR intervals (rMSSD) will be chosen as a reflection of vagal activity to prescribe the workout intensity [50]. In this regard, the natural logarithm of rMSSD will be calculated to make parametric statistical comparisons assuming a normal distribution. For establishing the training intensity and load, a 7-day rolling average measure (LrRMSSD7day-roll-avg) will be utilized. Subsequently, the scoring obtained will be contrasted in the smallest worthwhile change (SWC) to analyze if the daily result is inside SWC upper and lower limits, calculated as LnrMSSD reference week mean ± 0.5 × SD [51, 52]. The reference week of the first 4 training weeks will take the limits created in the baseline week, and in the rest of the program, an updated measure will be carried out every 4 weeks with the SWC for the past 4 weeks, because of the influence of exercise in participants cardiac autonomic modulation [53].

In this regard, when the daily LnrMSSD fell inside the limits created by the SWC patients will perform high-intensity training characterized by a cardiovascular intensity from 80 to 95% of their reserve HR (increasing a 5% every four weeks) and a weighting load from 70 to 85% of their RM (increasing the load 5% ever mesocycle, four weeks). Whereas if any day patients’ scoring fell out of the SWC, they will train at the same intensity as the PEG (Fig. 2).

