#### Physiological outcomes

##### Cardiotoxicity measurements

Cardiotoxicity will be assessed at the hospital to have a more exhaustive control and safety of the participants and at the end of the program. On the one hand, ç hemograms will be carried out to assess of High-Sensitivity Cardiac Troponin, Troponin I, N-terminal portion of B-type natriuretic pro-peptide (NT-proBNP), Troponin T due to their predictive values of cardiac damage in patients under the effects of chemotherapy [54, 55]. Although these variables were primarily planned in the trial registration, the hospital will be only able to assess High-Sensitive Cardiac Troponin and NT-proBNP.

In addition, an echocardiogram will be performed to measure the left ventricular ejection fraction and GLS due to its modification caused by cardiotoxicity [56–58] together with mean and maximum aortic valve gradient, ventricles’ diameters and thicknesses and valve velocities because their possible aortic stenosis risk [59]. Moreover, a resting electrocardiogram will also be performed on each patient to obtain values for heart rate, heart rhythm, heart rate variability, I-axis and aVF, Q-T interval, QRS complex, S-T segment and T-wave [60].

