Relatedly, the second aspect to highlight is the novelty of the exercise interventions compared to ones perform so far analyzing cardiotoxicity variables. To date, from our perspective, is the first study that will apply high and moderate to high-intensity cardiovascular and resistance training in breast cancer patients to analyze the cardiotoxicity effects, among others. Furthermore, except for one study protocol recently published [128] and a few studies in rats [129, 130], it would be also one of the first of including resistance training with so high weight and volume loads. Moreover, regarding exercise timing, the exercise programs focused on the improvement of cardiotoxicity variables such as LVEF, GLS, or troponin, most of the studies are carried out during breast cancer patients’ treatments [131] and not after them as our study will perform. However, cardiac abnormalities in breast cancer patients may appear within the first year after the end of chemotherapy, in case of early cardiotoxicity, or after several years following the completion of treatment (median of 7 years) [4]. Accordingly, to improve patients' cardiorespiratory fitness, troponin and GLS values and maintain the levels reached by acquiring physical exercise habits, in the current study patients have recently finished chemotherapy and radiotherapy to prevent the potential early and late cardiotoxicity. We will try to teach patients how to train during the 16 weeks of the exercise programs and to generate positive and self-determination experiences through exercise [132]. So that, we will promote exercise adherence to continue exercising even after its end knowing their cardiovascular and resistance levels at the end of the programs. Moreover, maybe if exercise programs are developed uniquely during chemotherapy or before it, patients can associate exercise to unpleasant cancer treatments or phases being unlikely to maintain exercising after treatments.

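### The only cardiac exclusion is dated to before chemotherapy, so severe heart disease that arose during or after treatment does not bar a patient from high-intensity exercise

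*Protocol article*

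**What the plan says.** All references are to the protocol article.

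- **Entry.** Under Recruitment and eligibility, chemotherapy and radiotherapy must both have been received and completed. A patient is excluded if "d) they have finished the cancer treatment more than 5 months ago", so entry falls within five months of the end of treatment.
- **Cardiac exclusion.** The only criterion that mentions the heart is "c) they have severe heart disease before chemotherapy". The other six exclusions concern planned surgery, HER2 status, time since treatment, metastasis, injury and psychiatric illness.
- **Order of events.** Randomization and allocation states: "Before baseline assessments, participants are randomly assigned to one of the three groups".
- **Cardiac tests.** Cardiotoxicity measurements lists blood markers, an echocardiogram and a resting ECG as outcomes and gives them a safety purpose: "Cardiotoxicity will be assessed at the hospital to have a more exhaustive control and safety of the participants". No finding is linked to exclusion or withdrawal.
- **Exercise dose.** PEG patients start at 65% and "will end with an intensity of 80% of their reserve HR". HRVG patients do "high-intensity training characterized by a cardiovascular intensity from 80 to 95% of their reserve HR" when the HRV value lies inside the individual limits, and train at PEG intensity otherwise.
- **Acknowledged risk.** The Background names heart failure, infarction and arrhythmia among the cardiac consequences for these patients. The Discussion says that "cardiac abnormalities in breast cancer patients may appear within the first year after the end of chemotherapy".

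**The concern.** The criterion is stated explicitly, but its time qualifier points to the wrong moment. What decides whether a woman can safely train at these intensities is her heart at enrolment, after the treatment that the article itself describes as cardiotoxic. A patient whose heart was sound before chemotherapy and is severely diseased at entry meets no exclusion.

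Patient safety is the main issue. Both exercise arms train remotely at intensities reaching 80% or more of reserve heart rate.

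A second consequence is possible but not shown. If severe disease is first seen at baseline tests, allocation has already happened. The team must then either keep an unsuitable patient in her arm or remove her after randomisation. If removals differed by arm, for instance because a control patient with the same finding could safely stay, the comparison between arms could be affected.

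**Working it through.** No stated figure needs to be reproduced. The check is a reading of the criteria in sequence, plus simple arithmetic on exposure.

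**Step 1: follow one patient through the criteria.** Take a woman aged 18 to 65 with luminal or triple-negative, non-metastatic disease. She finished chemotherapy and radiotherapy within the last five months, had no heart disease before chemotherapy, and has severe heart disease now.

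| Exclusion | Subject | Does it apply? |
|---|---|---|
| a | surgery scheduled during the study | no |
| b | HER2-positive disease | no |
| c | severe heart disease, before chemotherapy | no, hers came later |
| d | treatment ended more than 5 months ago | no |
| e | metastatic cancer | no |
| f | injury preventing participation | no, it names injury only |
| g | severe psychiatric illness | no |

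She meets all the inclusion criteria and none of the exclusions.

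**Step 2: can the planned tests act as an entry screen?** Randomization and allocation puts allocation before the baseline assessments. The ECG and echocardiogram are part of those assessments, so as written they come after the patient has an arm. They may reveal the disease before training starts, but no eligibility rule refers to them.

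**Step 3: what would she be asked to do?**

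- PEG: 65% rising to 80% of reserve heart rate.
- HRVG on days inside the limits: 80%, increased by 5 points every four weeks. Over 16 weeks this gives 80, 85, 90, 95, matching the stated range.
- HRVG on days outside the limits: PEG intensity. The HRV rule lowers the load but does not withhold exercise.
- All arms: under Cardiorespiratory fitness measurement, the treadmill test raises speed and incline every three minutes until the patient decides that she is too fatigued to go on. Outcomes applies the evaluations to all three groups, so control patients take this test too.

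**Step 4: exposure per patient so admitted.** No allocation ratio is stated, so equal allocation of the 90 patients is assumed (30 per arm).

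- Chance of an exercise arm: 60 / 90 = 2/3.
- Chance of HRVG: 30 / 90 = 1/3.
- Scheduled sessions: 14 weeks × 3 = 42 on the duration stated at the start of Physical exercise programs, or 16 weeks × 3 = 48 on the mesocycle schedule in the same section.

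**Step 5: is disease after treatment plausible on the article's own terms?** The Discussion places early cardiac abnormalities in the first year after chemotherapy. Entry is within five months of the end of cancer treatment. The two clocks differ: if radiotherapy followed chemotherapy, more than five months may have passed since chemotherapy ended. The entry period therefore cannot be said to lie wholly inside that first year. This does not weaken the point, since a longer interval leaves more time for disease to appear.

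The article gives no rate of severe heart disease arising during or after treatment. None is assumed, so no expected number of patients is calculated.

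**The case against.** The strongest reply is that the time qualifier is deliberate. The trial studies treatment-related cardiotoxicity. Dating the exclusion to before chemotherapy removes pre-existing disease and keeps treatment-related change in the sample. On that reading the article is only silent about current severe disease, and clearance and withdrawal rules may stand in a fuller protocol that is not shown. The intent is plausible, and the absence of a withdrawal rule is not counted here. But keeping cardiotoxicity in the sample does not require admitting severe disease, and the printed rule does admit it.

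The second reply is that several safeguards stand between eligibility and harm. An oncologist and a radiologist select patients, hospital tests take place before the intervention, the first mesocycle uses the lowest intensity, and sessions are supervised with live heart-rate monitoring. This largely stands. Harm would require the clinician to refer such a patient and the team to train her despite abnormal findings. The safeguards lower the probability and keep the point from being graded more severely. None of them makes the patient ineligible.

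Third, the supporting statements are general. The article speaks of abnormalities that may appear and of risk in survivors overall, not of severe disease within five months. That is correct. They show that the gap concerns a risk the authors recognise; they do not measure it.

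**Conclusion.** The concern holds. Applied as written, the eligibility rule admits a patient with current severe heart disease of later onset than the start of chemotherapy, and she can be allocated to exercise at up to 80% (PEG) or 80 to 95% (HRVG, on days within limits) of reserve heart rate. This rests on the wording of the criteria and the stated order of randomisation and baseline assessment.

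The number of patients affected cannot be derived from the article. The per-patient figures (2 in 3 for an exercise arm, 1 in 3 for HRVG) depend on equal allocation; the session range of 42 to 48 depends on which programme length applies. They describe exposure, not expected harm. The effect on validity is only a possibility and depends on removals differing by arm. The point should be fixed, mainly for patient safety.

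**What to change.** For patients still to be enrolled, reword exclusion (c) as: *severe heart disease before chemotherapy, or present at enrolment*. Judge it on the resting ECG and echocardiogram already planned, read before randomisation. Only these two tests need to move ahead of allocation. Mild or subclinical cardiotoxic change should stay eligible, because the trial sets out to study it. What counts as severe remains for the investigator and the hospital team to define.

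The cost is a protocol amendment during ongoing recruitment, probable ethics committee review, the registry update that Ethical approval and registration already provides for, and earlier scheduling of two tests. No new procedure is added. The drawbacks are that a few patients may not be enrolled, that findings will not extend to women with current severe heart disease, and that those already randomised entered under the narrower exclusion, which should be reported.
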